#### Couples health screening visit

Couples enrolled in the Igugu Lethu study may schedule an appointment for a couples’ health screening visit at any time after the first group session, once they feel ready to participate in HIV testing and counselling together. The health screening visit will only proceed if, on the appointment date, both partners consent to HIV testing together. All other tests offered are optional. The visit will be conducted to avoid days when the female partner is menstruating. If couples report testing for HIV together as a couple at an alternate venue during the Igugu Lethu study, the couple will be encouraged to undergo the couples health screening visit before completion of study participation.

Informed consent will be taken for each of the health screening procedures (HIV test, random blood glucose (RBG) tests, blood pressure and body mass index (BMI) measurements, and self-sampling for sexually transmitted infection testing) at the start of the visit from each couple by the study counsellor.

At the couples health screening visit, height and weight will be measured, and BMI will be calculated for each partner using an electronic scale (Scale Digital BMI 1110H SOAMAA). Blood pressure will be measured by a study counsellor using Brand Axcess BP 1359 devices while the participant is seated, and three consecutive readings will be averaged [35], in line with recommendations by the American Heart Association.

The counsellor will explain the need for self-collected samples to test for chlamydia, gonorrhoea, and trichomoniasis. The counsellor will explain and demonstrate the procedure for obtaining the self-collected vaginal swabs to the female member of the couple and will ask her to self-collect two sequential vaginal swabs behind a medical curtain for privacy. A nurse will be on call if assistance is needed. For men, the counsellor will explain and demonstrate how to obtain a self-collected penile swab, rotating a flocked swab twice around the full circumference of the penis at the *coronal sulcus*, the junction between the glans and the shaft of the penis. A urine sample will be requested for testing *C. trachomatis, N. gonorrhoeae*, and *T. vaginalis* infections. After the sample collection, samples will be transported to a commercial accredited laboratory in cool boxes. The couples health screening questionnaire includes questions on the acceptability of self-sampling.

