The counsellor will give all other results with appropriate interpretation, counselling messages and Department of Health information pamphlets to the couple. The NCD counselling messages will be based on WHO Guidelines for Primary Care in Low-Resource Settings [36], and Section 4.1 of the Standard Treatment Guidelines and Essential Medicines List for South Africa-Primary Health Care Level 2018 Edition [37]. The counsellor will use the BMI-based CVD risk Framingham Heart Study tool to calculate for participants their 10-year risk of a fatal or non-fatal cardiovascular event (myocardial infarction or stroke), according to age, sex, blood pressure, presence or absence of diabetes, and smoking status, and will use this score when counselling about lifestyle changes [38]. In addition to lifestyle counselling, active referral to the clinic will be made for individuals who have systolic blood pressure (SBP) ≥ 180 mmHg or diastolic blood pressure (DBP) ≥ 110 mmHg, and a letter of referral (passive referral) will be given to those with moderate hypertension (SBP: 160–179 mmHg, DBP 100–109 mmHg), suggesting they have a repeat blood measure in 2 weeks. For individuals with an RBG result of > 11.0 mmol/L, we will ask questions to determine if they have symptoms indicating diabetes. If their answers indicate symptoms, they will be actively referred to a clinic. If they do not report symptoms, they will be given a letter of referral (passive referral) requesting that the clinic tests their fasting blood glucose level. Local clinics have agreed to receive such referred cases.

A date for the return (STI results) visit will be scheduled before the couple leave the health screening visit. The preferred mode of contact (e.g. telephone call, text or WhatsApp Messenger or in persons) and ideal hours for contact will be recorded for each couple, so that they can be notified whether they need to physically attend their STI results appointment when their STI results and those of their partner become available. Couples will be informed that if we find a curable STI and three attempts to contact them by their preferred mode of contact fail, a study staff member will attempt to find them. Couples who are referred to clinic during the couples’ health screening visit because one or more test results are ‘out of range’, will be asked to return to the appointment in 2 weeks regardless of positive or negative STI results.

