### Statistical considerations

#### Sample size, accrual, follow-up

In the Uthando Lwethu study, 39% of the intervention arm (65/168 couples) had taken up testing together for HIV by 4-months follow-up. A sample size of 180 couples in the Igugu Lethu study provides more than 85% power, at the 5% level, to detect a 40% increase in the proportion testing together, i.e. change from 39 to 55% between the two versions of the intervention, and allow for 5% lost to follow-up or break-up by 4-months.

We aim to accrue the sample of couples over approximately 16 months of active recruitment. Given the continued SARS-CoV-2 pandemic, changes in public health and research-related restrictions may mean a slower rate of recruitment. We will recruit in waves and aim to have approximately 20 couples participate in a round of intervention activities, and will continue to conduct intervention rounds until we achieve our goal of 180 couples. We will follow the couples for a total of 4-months from the date of the first group session in each intervention round.

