#### Data analysis

Our primary analysis will compare the proportion of couples who test for HIV in Igugu Lethu with the proportion of couples in the intervention arm of the Uthando Lwethu study who tested for HIV within 4-months of follow-up, unadjusted, using a chi-square test. We will also compare this cohort’s baseline characteristics with the Uthando Lwethu cohort’s baseline characteristics. If there are substantial differences, the comparison will be adjusted for these characteristics using logistic regression.

We will also consider the proportion of couples taking up each of the other non-HIV tests offered as part of the couples health screening. We will calculate descriptive statistics and apply chi-square tests to examine concordance in test results within couples and the secondary outcomes listed a)-i). The acceptability of self-sampling for STI testing by men and women will be examined using responses to Likert scales asked as part of the couple’s health screening questionnaire, separately for men and women, and compared within couples.

The content of the intervention is designed to enhance couples’ levels of communication, intimacy, and other positive relationship characteristics. Therefore, we expect that as couples’ levels of positive relationship characteristics increase, they will be more likely to participate in couples HIV testing. To evaluate the extent to which relationship dynamics are associated with couples’ uptake of HIV testing together, we will describe the change in relationship scores between baseline and 4-weeks, and baseline and 4-months. We will test for associations between these score changes and the HIV couples testing outcome using logistic regression. In addition, the acceptability of the intervention and study participation will be explored through thematic analysis using findings from individual, semi-structured process interviews, and descriptive statistics of responses to the process evaluation questions asked of all participants as part of the 4-month questionnaire.

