DNA yield from stored penile swabs will be used to determine whether men’s self-sampling around the coronal sulcus is a feasible method for sample collection, an important finding for future studies. Assuming sufficient DNA for 16S analysis and protein for proteomic analysis from the stored swabs, vaginal and penile microbiome composition will be described. For functional analysis, iBAQ values of proteins with the same Gene Ontology IDs will be aggregated. Basic R functions and the ggplot2 R package will be used for data manipulation, transformation, normalisation and generation of graphics. Data will be further explored using principal component analysis using the mixOmics R package, unsupervised hierarchical clustering using the Complex Heatmap package and FlipPlots. The limma R package will be used to identify differentially abundant taxa, proteins and gene ontologies within couples and between groups defined by age, STI status, and 16S profiles.

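### The microbiome analysis compares age groups although participants' ages are recorded; a continuous age term would avoid a loss of information whose size depends on unstated groups and ages

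*Protocol article*

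**What the plan says.** The last paragraph of Data analysis assigns limma to the search for differential abundance within couples and "between groups defined by age, STI status, and 16S profiles". Age is thus named as a variable that forms groups. The number of groups, the cut-points and a reason for grouping are not given.

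Individual age is available. Under Couples health screening visit, the counsellor calculates a 10-year cardiovascular risk for participants "according to age, sex, blood pressure, presence or absence of diabetes, and smoking status". Eligibility is 18 years and over, with no upper limit.

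Swabs come from a subset of the cohort. "The health screening visit will only proceed if, on the appointment date, both partners consent to HIV testing together", and the other tests at that visit are optional. The microbiome work is further conditional on enough DNA and protein being recovered. It serves the last of the four secondary objectives, which is exploratory. The article states no swab count and no power for it.

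**The concern.** Cutting a measured quantity into groups removes the differences within each group. Two participants several years apart but in the same group count as identical, while two close in age on either side of a cut-point count as different. If abundance changes gradually with age, part of the signal becomes residual noise.

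Finding the cut-points in a fuller analysis plan would not settle this, because no choice of cut-points recovers the variation within groups. What is at stake is the chance of detecting an age gradient in the penile or vaginal microbiome, in a modest sample and with many features examined.

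**Working it through.** **The plan's own figure.** The only power statement concerns the primary comparison: "A sample size of 180 couples in the Igugu Lethu study provides more than 85% power, at the 5% level", for a "change from 39 to 55% between the two versions of the intervention". The inputs are 168 historical couples, of whom "39% of the intervention arm (65/168 couples) had taken up testing together for HIV by 4-months follow-up"; 180 new couples, with the plan to "allow for 5% lost to follow-up or break-up by 4-months", so 180 × 0.95 = 171; and a test that is "unadjusted, using a chi-square test", taken as two-sided.

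Power = Φ{[|p2 − p1| − 1.96·√(p̄(1 − p̄)(1/n1 + 1/n2))] / √(p1(1 − p1)/n1 + p2(1 − p2)/n2)}.

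- n2 = 171: 84.2% with p1 = 0.39, and 85.6% with p1 = 65/168.
- n2 = 180: 85.1% and 86.5%.

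The stated figure is reproduced to within a point or so. It is not in dispute, and it says nothing about the microbiome analysis.

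**Swabs per site.** Uptake × couples retained:

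- Target uptake: 0.55 × 171 = 94.
- Historical uptake: 0.39 × 171 = 67.

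Counting all 180 couples gives 99 and 70. Each figure assumes that every tested couple gives a usable swab, so refusals and poor yield reduce it.

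**Information lost by grouping.** For a linear effect, the information on the slope is proportional to the variance of the covariate, and grouping keeps only the between-group part:

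loss = 1 − Var(group mean age) / Var(age).

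- Normal ages, two equal groups: retained 2/π = 0.637, loss 36%.
- Normal ages, three equal groups: retained (2/3)·(φ(z)/(1/3))², with z the 1/3 quantile, = 0.793, loss 21%.
- Uniform ages, g equal groups: loss 1/g².
- Other cases: simulation with 2 million draws. The right-skewed ages are 18 plus a gamma variable of shape 2.

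| Age shape (assumed) | 2 groups | 3 groups | 4 groups | 5 groups |
|---|---|---|---|---|
| Uniform | 25% | 11% | 6% | 4% |
| Normal | 36% | 21% | 14% | 10% |
| Right-skewed | 45% | 28% | 21% | 16% |

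These are illustrations, not bounds. A more extreme skew (18 plus an exponential variable) gives 52% with two groups.

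**What this means at 94 swabs.** With near-normal ages the effective number is 94 × 0.637 ≈ 60 (two groups) or 94 × 0.79 ≈ 74 (three groups). To illustrate, take the correlation between age and log abundance that has 80% power with continuous age, for a single feature at two-sided 0.05: r = tanh((1.96 + 0.84)/√(94 − 3)) = 0.29. Multiply r by the square root of the retained fraction and recompute power by Fisher's z:

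- Three groups: about 70%.
- Two groups: about 60%.

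At 67 swabs the correlation with 80% power is 0.34, and power falls to 69% and 60%. These figures treat the group comparison as a single one-degree-of-freedom contrast; an unordered comparison of three groups spends one more.

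**The case against.** The sentence is a single line in a condensed journal article, and the word for groups may be shorthand for factors to be examined. The coding of a covariate in a design matrix often belongs in an analysis plan, which is not shown here. That stands as a reason not to fault missing cut-points. It does not remove the point, because grouping age is what the text states.

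Groups can also reveal a threshold or a rise and fall with age that a straight line would miss, and the shape of any age effect over an open-ended adult range is unknown. This stands against insisting on a linear term. It does not favour grouping, because a low-order spline follows such shapes while still using age in years.

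A reader might go further and infer that age, STI status and 16S profile are examined one at a time, so that an age difference could pass for an STI difference. The text does not support that. It lists the three variables in one sentence and does not say whether they are fitted singly or jointly.

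Finally, differences by age are neither a stated objective nor a listed outcome. The objective and outcomes concern microbiome characteristics and concordance within couples. This is correct, and it limits how much the point matters.

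**Conclusion.** The point holds as a minor one. The plan states a less efficient treatment of age where a better one is available from data it already holds. The loss is about 21% to 36% of the age information for three or two equal groups with near-normal ages, and about 4% to 45% over two to five groups and the three age shapes tabulated. All of this assumes a roughly linear age effect and equal-sized groups.

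A reader might take a fifth to a third as a fixed loss, or 94 as the swab count. Neither is supported. The first depends on a group number and age distribution that the article does not give. The second requires the uptake target to be met with no refusals and no failed samples. The correlations, and the single-feature 0.05 threshold in the power illustration, are also assumptions made here; the article gives neither.

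The consequence is confined to the exploratory microbiome analysis. The primary comparison of testing uptake is unaffected.

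**What to change.** In the microbiome paragraph of Data analysis, replace the reference to groups defined by age with age in years as a continuous term in the limma design, fitted separately for penile and vaginal swabs. If non-linearity is a concern, use a spline with few degrees of freedom. Preferably put age and STI status in the same model and say so; this is a clarification, not the correction of a stated error. Keep age groups for plots and heatmaps only.

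The cost is one line of wording and the matching code, with no new data or visits. There is a trade-off: a spline spends one or two extra degrees of freedom, while a purely linear term could miss a non-monotone pattern. The choice should be written down before the swab data are examined.

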#### Ethical considerations

Public involvement in community-based health research in South Africa is well-established and monitored. Community involvement is integral to the development of all research proposals supported by HSRC at the HSRC Sweetwaters site. A community advisory board (CAB) includes representatives of the provisional health and welfare departments and municipal government, and community leaders. The CAB meets quarterly with Sweetwaters senior staff to discusses all study proposals and ongoing projects, community research priorities, and community issues that arise.

The Igugu Lethu study has convened a dedicated community working group (CWG) of 8–10 members including at least one CAB member. The CWG will liaise closely with the study team throughout the study, including through quarterly meetings. The CWG received additional training to facilitate contributions to decisions about study-specific operations, particularly focusing on ensuring feasibility and acceptability in the communities they represent. The study was approved by the HSRC Research Ethics Committee, South Africa (2/19/10/11c), the Faculty of Medicine Research Ethics Committee, University of Southampton, UK (53709), and the Health Research Committee of the KwaZulu-Natal Provincial Department of Health (KZ_202009_041). A data monitoring committee was not required for this low-risk behavioural intervention cohort study.

#### Informed consent

The HSRC Sweetwaters site is experienced in obtaining consent from couples in prior studies [9, 42]. Before a recruiter administers the screening questionnaire over the phone, verbal consent will be recorded. When the call has ended, the audio recording will be uploaded by the recruiter to a password protected, encrypted computer file, labelled with the individual’s study ID, stored separately from the study data.

Written informed consent will be required before conducting the baseline screening, for the couples health visit and for process interviews (invited participants and staff). Each member of the couple will consent individually. If participants cannot provide a signature due to literacy issues, a witness will sign on their behalf. The participant information and consent documents will be available in English and isiZulu. All participants will be given a copy of each participant information and consent document they sign to take home. Separate consent will be sought from couples to audio record their couples counselling sessions for quality assurance and for research purposes, and to audio-record process interviews. As part of the informed consent process for the couples health visit, participants will be asked to consent to their contact details and the outcomes of their health check being shared with the Department of Health (DoH). This is per the site’s memorandum of understanding with the DoH, 14/8/3/1/2179 so that the DoH has a more complete medical history for each participant and can provide uninterrupted care. Results of the health screening visit will only be shared with the study counsellor by the participants themselves. Couples may withdraw from the study at any time.

#### Risks

The possibility exists that participating in the study might lead to tension, conflict and/or possible violence between the partners. The risk for participants primarily stem from 1) discomfort or distress as a result of the personal and sensitive nature of the assessment interviews and intervention sessions or 2) loss of confidentiality. For the optional procedures of HIV and STI-testing, there are the following risks: 1) there are small risks associated with the finger prick necessary for use of the rapid HIV test, 2) risks associated with finding out that oneself or one’s partner is HIV-positive/STI-positive, 3) the possibility that some participants may feel pressure to test for HIV. Finally, there is additional potential for risk should the study team become aware of situations in which HIV/STIs transmission could occur.

Risks to subjects will be minimised by: 1) training of staff in the ethical conduct of research and all confidentiality-protecting procedures 2) training of staff in issues specifically pertaining to couples in this setting (e.g. potential for coercion for women participating, potential for partner violence, possible coercion to test for HIV), 3) close monitoring of any adverse events with appropriate IRB reporting and 4) referral to social workers if a staff member has concerns about a participant’s safety or well-being. One area where confidentiality cannot be guaranteed by the study team is information shared by participants in in group sessions. However, we will directly address the importance of respecting group members’ confidentiality at the start of the session when study facilitators and participants agree ground rules.

Additional measures are needed to protect each participant’s confidentiality from their partner. In previous couples-focused research, we have developed procedures that include conducting individual data collection interviews by a gender-matched interviewer in a private room, ensuring that each member of couple does not have contact with the interviewer who administered the baseline and follow-up surveys to their partner. During the informed consent process at the baseline screening, we will discuss with participants the possibility that their partner might ask about their answers to certain questions or issues they discussed. Interviewers will be trained to discuss with participants ways of coping with this situation if the participant they are consenting expresses concern or distress about this matter either during consent, the administration of a questionnaire, or after a questionnaire is completed. Interviewers and intervention staff will also be trained in the identification of, and proper response to, issues of coercion or abuse, and will be know how to refer participants for domestic violence assistance. A list of community-based resources for couples is regularly updated, and will be offered to each couple at all visits.

#### Risk of HIV disclosure

All staff will be familiar with Confidentiality: Protecting and providing information (Booklet 5) from the Health Professions Council of South Africa’s guidelines for HIV disclosure [43]. The South African Medical Association recommends that health care workers do not disclose the HIV status of an individual to third parties (including family, sexual partners, and employers) unless the patient has provided informed consent. At present, there is no law in South Africa forcing people to disclose their HIV status to their partner. Should the situation arise where it is established that one partner has not disclosed their HIV-positive status to their partner and they are not on antiretroviral therapy, study couples counsellors will offer support to the participant to disclose to their partner and refer for further support if needed. The study team would also actively facilitate linkage to care to initiate ART, counsel to abstain from sex or consistently use condoms.

